### 9.4. Medico-Economic Statistical Analysis

The endpoint of the medico-economic analysis will be the cost per serious clinical event avoided within 90 days and will be expressed as the differential cost-efficacy ratio: DCRR = Δ Costs/Δ Efficacy.

Statistical analysis specific to the medico-economic section will be carried out based on a decision tree. 

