Several strategies have therefore been devised to limit the use of CTPA, based on the formalized assessment of clinical probability (CP) and/or by modifying the cut-off value for D-dimer tests. Yet, each of these strategies is based on a different and specific method of assessing CP: the PERC (pulmonary embolism rule-out criteria) and implicit assessment for ruling out PE on clinical criteria [8,9,10], the YEARS rule or the adapted Wells score for ruling out PE on CP-adjusted D-dimer cut-off [11,12], and the revised Geneva score or the Wells score for ruling out PE on age-adjusted D-dimer cut-off [13,14]. This makes them difficult to use and combine, and can lead to non-expert physicians misusing these rules or relying solely on their empirical assessment, thereby exposing themselves to the risk of a misdiagnosis (loss of reliability) or inappropriate use of CT (loss of efficacy). 

We have developed and validated a score that combines all these possibilities into a single rule: 4PEPS (four-level pulmonary embolism probability score) [15]. Based on ISTH recommendations and depending on the prevalence of VTE in the population, the acceptable number of false negatives has been set to 2% [16]. Using 12 variables, 4PEPS defines four levels of CP that rule out a PE, namely (1) based only on clinical data (very low CP: PEPS < 0), (2) based on a D-dimer level < 1000 µg/L (low CP: PEPS ≥ 0 et < 5), (3) based on a D-dimer level with an age-adjusted cut-off value (moderate CP: PEPS ≥ 5 and <12), or (4) the diagnosis cannot reliably be ruled out based on a D-dimer test (high CP: PEPS ≥ 12) (Table 1). Assessed retrospectively based on large databases, the 4PEPS strategy seems to be more efficient and just as safe as the other strategies [15,17,18]. 

Our research hypothesis is that a diagnostic strategy based on 4PEPS will help reduce the use of thoracic imaging without increasing the risk of serious adverse events linked to the diagnostic approach. 

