## 8. Medico-Economic Analysis

The medico-economic analysis will be performed following the recommendations of the French National Authority for Health (HAS) (https://www.has-sante.fr/portail/jcms/r_1499251/fr (accessed on 1 November 2022)) and the CHEERS (Consolidated Health Economic Evaluation Reporting Standards) statement [25]. A cost–efficacy analysis will be performed, aimed at comparing the efficacy of applying the 4PEPS strategy against usual practices in terms of cost for each serious event avoided, from the perspective of health insurance. The timescale will be 90 days corresponding to the evaluation period of the efficacy endpoint.

The result will be shown as a differential cost–efficacy ratio and expressed as a cost per serious event avoided within 90 days (serious adverse event of PE testing, PE-related death, thromboembolic event, or major bleeding). This evaluation will be performed at D90 via a telephone call using a standardized questionnaire.

The evaluation of costs will concern the use of hospital and outpatient treatments and medical equipment (medications and medical devices). 

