### 9.2. Primary Statistical Analysis

The two main endpoints will be analyzed in a hierarchical manner. Firstly, non-inferiority will be analyzed on the safety endpoint with a non-inferiority limit set at 1.5%. If and only if confirmed, superiority analysis on the efficacy endpoint will be performed. Analyses will be performed using a mixed-effects logistic regression in line with recommendations for this type of study [26]. Missing data will be analyzed in order to determine whether they are informative and whether they are likely to cause a potential screening or information bias. 

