### 10.1. Safety Endpoint

Considering the participation of 20 centers, 10 centers in each group, an alpha risk of 5%, a power of 80%, a clinical event rate of 1.5% at 3 months in both groups, a non-inferiority limit of 1.5%, an intra-center correlation coefficient of 0.002, and a rate of patients lost to follow-up or non-analyzable of 5%, it will be necessary to enroll 2560 patients, 1280 in each arm.

The serious clinical event rate at 3 months will be estimated by taking into account a risk of adverse event related to diagnostic testing of 0.1%; a PE prevalence of 14% [10,11]; a risk of thromboembolic events in patients for whom the diagnosis is ruled out estimated at 0.8% [15] and in patients for whom the diagnosis is made (14% of the population); a PE-related death rate of 2% [28,29]; major bleeding of 2% [28]; and thromboembolic recurrence of 2% [29]. The intra-center correlation rate at 0.002 and the non-inferiority limit at 1.5% will be estimated on the basis of a recent French study [30].

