The hierarchical analysis applied in SPEED&PEPS will allow us to address the questions of efficacy and safety without increasing the alpha risk through multiple tests. If our research hypothesis is confirmed, this will have a major impact for patients and for public health. For patients, the reduction in the use of imaging tests will make it possible to limit the cumulative radiation exposure, the impact of which is now known in terms of the risk of radiation-induced cancer, in particular breast cancer, for women. It will reduce the time it takes to manage patients with suspected PE in the emergency department, as patients that undergo thoracic imaging take an average of 4 h longer to treat than those who do not require it. Our study will thus have an indirect impact on other patients by limiting the overcrowding of emergency departments. Lastly, given the frequency of suspected pulmonary embolism in emergency departments and the very high usage rate of CT angiographies (80% in a recent observational study [10]), the SPEED&PEPS study should result in substantial savings in terms of the direct cost of diagnostic investigations and the indirect cost of hospitalizations due to waiting times or delayed harmful effects. We expect the cost per serious clinical event avoided in relation to the diagnostic approach to be very favorable compared to current practices.

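### The only named economic endpoint, cost per serious event avoided, has a planned denominator of zero and would be unstable if event rates are equal

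*Protocol article*

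**What the plan says.** Section 9.4 defines the economic endpoint: "The endpoint of the medico-economic analysis will be the cost per serious clinical event avoided within 90 days". It adds that this "will be expressed as the differential cost-efficacy ratio: DCRR = Δ Costs/Δ Efficacy" and that the analysis will be based on a decision tree. Section 3.2 names the same ratio at 90 days. Section 8 gives the unit of the denominator, with the result "expressed as a cost per serious event avoided within 90 days (serious adverse event of PE testing, PE-related death, thromboembolic event, or major bleeding"; these components are in essence those of the primary safety composite in Section 3.1. Section 8 also commits the analysis to national health-authority recommendations and to CHEERS.

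For that composite, Section 10.1 assumes "a clinical event rate of 1.5% at 3 months in both groups". The hypothesis in Section 1 is that imaging will fall "without increasing the risk of serious adverse events linked to the diagnostic approach", and in Section 9.2 "non-inferiority will be analyzed on the safety endpoint with a non-inferiority limit set at 1.5" percent. The Discussion (Section 12) says: "We expect the cost per serious clinical event avoided in relation to the diagnostic approach to be very favorable compared to current practices".

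**The concern.** The trial is planned to show less imaging (45% to 36%, Section 10.2) with no more serious events. The economic ratio has serious events avoided in its denominator, the quantity on which no difference is planned. The planned gain, fewer imaging tests, enters only through cost.

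A ratio whose denominator is centred near zero has three defects:

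- Its size is driven by noise in the denominator.
- Its confidence interval is unbounded whenever the interval for the denominator includes zero.
- Its sign is ambiguous. A saving with more events and an extra cost with fewer events both give a positive ratio, although they mean opposite things.

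At stake is the usefulness of the economic result if the trial succeeds as planned. Non-inferior safety, less imaging and lower cost would be a good outcome, yet the one named economic endpoint would summarise it poorly.

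**Working it through.** **Inputs.** From Section 10.1: 1.5% events in both groups, margin 1.5%, "10 centers in each group, an alpha risk of 5%, a power of 80" percent, intra-centre correlation 0.002, 5% loss, 1280 enrolled per arm. From Section 9.1: one-sided tests. From Section 10.2: imaging 45% against 36%.

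**The plan's own figures.**

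- *Event rate.* The components give 0.14 × (2% + 2% + 2%) + 0.86 × 0.8% = 0.840% + 0.688% = 1.53%, or 1.63% with the 0.1% testing risk. Only one rate is built, and it is used for both arms.
- *Sample size.* At one-sided 5%, the standard formula gives 812 per arm before clustering and 1018 to 1072 after clustering and loss, not 1280. At one-sided 2.5% it gives 1031 before clustering and 1280 to 1296 after clustering without loss. The mismatch is a separate matter. What counts here is that each version takes the true difference as zero.

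**Planned denominator.** 1.5% − 1.5% = 0.

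**Precision of the observed denominator.**

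- Analysed per arm: 1280 × 0.95 = 1216, or 121.6 per centre.
- Design effect: 1 + (121.6 − 1) × 0.002 = 1.2412.
- SE = √(2 × 0.015 × 0.985 × 1.2412 / 1216) = 0.00549, or 0.55 points.
- 95% half-width: 1.96 × 0.549 = 1.08 points, about 11 events per 1000.
- Chance of a difference within 1 event per 1000: P(|Z| < 0.001/0.00549) = P(|Z| < 0.182) = 0.144. In that range the ratio is more than 1000 times the per-patient cost difference in size.

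**Simulation with both true rates 1.5%** (beta-binomial, 10 centres per arm, 122 patients per centre, correlation 0.002, 200,000 runs):

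| Observed event difference | Share of trials |
|---|---|
| Favours 4PEPS | 47% |
| Exactly zero | 6% |
| Favours control | 47% |
| Within ±1.96 planning SE of zero | 96% |

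The document gives no costs. As an illustration only, assume a saving of 100 currency units per patient. With ties excluded, the central 95% of the simulated ratios runs from −122,000 to +122,000 per event.

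**Would a modest true reduction help?**

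- If the 0.1% testing harm fell by 20%, the true difference would be 0.02 points, or 0.0002 × 1280 = 0.26 events per arm. The observed sign would favour 4PEPS in 48.5% of trials and control in 45.6%.
- Suppose instead that diagnosed PE fell by 20%, from 14% to 11.2% (an assumption). Major bleeding at 2% of diagnosed patients would fall by 2.8% × 0.02 = 0.056 points, about one tenth of the SE.
- For the interval to exclude zero, the intervention rate would have to be near 0.6%. There SE = √((0.015 × 0.985 + 0.006 × 0.994) × 1.2412 / 1216) = 0.0046, and 1.96 × 0.0046 = 0.0090 = 1.5% − 0.6%. That is a fall of about 60%, which nothing in the document anticipates.

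**Quantities that stay defined at a zero event difference.** Incremental cost; incremental events; net monetary benefit, which with λ the value per event avoided becomes λ × 0 − ΔCosts = −ΔCosts; and cost per imaging test avoided, with a planned denominator of 0.09 × 1280 = 115 tests.

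**The case against.** A reader might infer that the ratio is undefined under the trial's own hypothesis, and that the Discussion contradicts that hypothesis. The document does not support either reading. The equal 1.5% rates are a sample-size assumption. The stated hypothesis is no increase, which allows fewer events. The Introduction and Discussion also give a mechanism for a reduction: less overdiagnosis, hence less unnecessary anticoagulation and bleeding. In observed data an exact zero would occur in only about 6% of trials, so the usual failure is instability, not division by zero. A saving with fewer events is a clear result (dominance), and the other combinations can be read once the quadrant is named. All of this stands, and it limits the point to instability.

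It can also be said that a condensed article leaves the handling of uncertainty to a fuller plan, and that the decision tree and the HAS and CHEERS commitments cover it. The absence of a bootstrap or a rule for near-zero denominators is indeed no finding. The choice of endpoint, however, is made here in three sections, and none of these commitments changes the denominator. A tree fed with the plan's rates returns zero; one fed with trial data inherits their noise. How the tree will be populated is not stated, so the simulated figures apply to a direct comparison of the two arms.

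Finally, the consequence is limited. The economic analysis lies outside the testing hierarchy, and no sample size or safety conclusion depends on it.

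**Conclusion.** The point holds as a weakness in the choice of endpoint. The planned denominator of the only named economic endpoint is zero. With equal true rates the observed denominator has an SE of about 0.55 points, either sign is about equally likely, and the ratio would have no bounded interval in about 96% of trials. The small reductions that the plan's own component rates suggest hardly change this. The Discussion's expectation sits uneasily with the equal planning rates but does not contradict a stated hypothesis.

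The figures rest on 1216 analysed patients per arm in equal-sized centres, an intra-centre correlation of 0.002 and a direct two-arm comparison. A cheap improvement is available; the primary conclusions are not affected.

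**What to change.** Change Sections 3.2, 8 and 9.4:

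- Make the main economic result the incremental cost per patient and the incremental serious events, reported separately.
- Add incremental net monetary benefit over a stated range of values per event avoided.
- Show joint uncertainty in cost and events on the cost-effectiveness plane, by a method that allows for clustering by centre.
- Keep cost per serious event avoided as a descriptive result with its quadrant named. Report it always: making it conditional on a significant event difference would select large observed differences and suppress it in most trials with equal rates.
- Cost per thoracic imaging test avoided may be added as supplementary. It should not replace the patient outcome, because it is a process measure.
- Reword the Discussion's expectation so that it fits the equal planning rates.

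The cost is wording only, with the same data. The headline is no longer a single ratio, and net benefit needs a range of values per event to be stated and justified in advance.

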## 10. Justification of the Number of People to Be Included in the Study

The number of patients to be included will be set to demonstrate in the intervention group versus the control group: (1) non-inferiority on the primary safety endpoint (the rate of patients during follow-up with a fatal PE, thromboembolic event, or major bleeding due to anticoagulant treatment) and (2) superiority on the primary efficacy endpoint (the usage rate of thoracic imaging). 

### 10.1. Safety Endpoint

Considering the participation of 20 centers, 10 centers in each group, an alpha risk of 5%, a power of 80%, a clinical event rate of 1.5% at 3 months in both groups, a non-inferiority limit of 1.5%, an intra-center correlation coefficient of 0.002, and a rate of patients lost to follow-up or non-analyzable of 5%, it will be necessary to enroll 2560 patients, 1280 in each arm.

The serious clinical event rate at 3 months will be estimated by taking into account a risk of adverse event related to diagnostic testing of 0.1%; a PE prevalence of 14% [10,11]; a risk of thromboembolic events in patients for whom the diagnosis is ruled out estimated at 0.8% [15] and in patients for whom the diagnosis is made (14% of the population); a PE-related death rate of 2% [28,29]; major bleeding of 2% [28]; and thromboembolic recurrence of 2% [29]. The intra-center correlation rate at 0.002 and the non-inferiority limit at 1.5% will be estimated on the basis of a recent French study [30].

### 10.2. Efficacy Endpoint 

Considering the participation of 20 centers, an alpha risk of 5%, a power of 80%, an intra-center correlation coefficient of 0.05, and a usage rate of thoracic imaging of 45% in the control group, it will be necessary to include 2128 patients to demonstrate a relative decrease (1-sided analysis) greater than or equal to 20% (an absolute decrease of 9%) between the control and interventional groups in the usage rate of thoracic imaging. 

The intra-center correlation coefficient will be set at 0.05, given that the use of imaging is strongly linked to professional practices, which themselves vary significantly between centers. We estimate that it will be 45% in the control group and 36% in the interventional group on the basis of a previous retrospective assessment [15].

This means the figures previously calculated (2560 patients) will be sufficient for the hierarchical analysis of this endpoint. Nevertheless, an analysis of the usage rate of thoracic imaging in the control group will be performed after the inclusion of 1500 patients, i.e., 750 patients in the control group. If this rate is lower than expected (<45%), a reassessment of the sample size will be performed in order to assure a power of 80% to demonstrate a relative decrease of at least 20% between the control and the interventional groups on the usage rate of thoracic imaging.

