## 5. Experimental Plan and Randomization

SPEED&PEPS will be an open-labelled cluster-randomized study, with 10 centers being allocated to the control group and 10 centers to the interventional group. Before randomization, participating centers will perform a preliminary assessment of the number of patients being investigated for suspected PE per month and of the rate of imaging test performed in patients suspected of PE in order to have an accurate idea of their baseline status [20]. These two criteria will be applied as stratification criteria during randomization to assure comparability between groups. 

SPEED&PEPS will be a pragmatic trial as confirmed by the PRECIS-2 rating of 42 out of 45 on the scale, with 0 corresponding to a fully explanatory study and 45 to a fully pragmatic study (cf. supplemental material) [24]. 

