## 9. Statistical Analysis

### 9.1. General Considerations 

Population characteristics will be described using their mean/standard deviation, median/interquartile range, or percent/95% confidence interval, as appropriate. Univariate comparisons will be made using Student’s, Mann–Whitney, or Fisher’s exact tests, as appropriate. The alpha risk will be set at 5%. All tests will be one-sided. Given that some proportions are expected to be small, confidence intervals will be calculated using the Clopper and Pearson exact method. 

The analysis will be performed using R software (R Foundation for Statistical Computing; 2008. http://www.R-project.org (accessed on 1 November 2022)) and its PropCIs and MASS add-ons (http://CRAN.R-project.org/package=PropCIs (accessed on 1 November 2022)). All objectives will be analyzed on the overall included population (intention-to-treat). A complementary per-protocol analysis will be performed, especially for the 4PEPS strategy in the interventional group. 

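### The efficacy sample size of 2128 does not follow from its own inputs: at ICC 0.05 with 10 centres per arm, power is about 50%, and adding patients cannot bring it to 80%

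*Protocol article*

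**What the plan says.** Section 10.2 (Efficacy Endpoint) sets out the calculation: "Considering the participation of 20 centers, an alpha risk of 5%, a power of 80%, an intra-center correlation coefficient of 0.05", with thoracic imaging in 45% of control patients and 36% of intervention patients. Its result is that "it will be necessary to include 2128 patients to demonstrate a relative decrease (1-sided analysis) greater than or equal to 20" per cent. On the correlation it says "The intra-center correlation coefficient will be set at 0.05", because imaging depends strongly on local practice, which differs between centres. It then compares the result with the number derived for safety in section 10.1: "This means the figures previously calculated (2560 patients) will be sufficient for the hierarchical analysis of this endpoint".

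The layout comes from section 5, "with 10 centers being allocated to the control group and 10 centers to the interventional group", and from section 10.1, 1280 patients per arm. Section 9.1 makes all tests one-sided at 5%. Section 9.2 plans a mixed-effects logistic regression. Section 10.2 also plans a look at the control-group imaging rate after 1500 inclusions, with a new sample size if that rate is below 45%, in order to secure 80% power.

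**The concern.** In a cluster trial with a fixed number of centres, patients added to the same centres bring less and less information. Once centres are large, precision is set by the number of centres and the ICC. Ten centres per arm with an ICC of 0.05 is few for a 9-point difference, so a finite requirement of 2128 needs checking.

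Reduced imaging is one of the two parts of the primary objective. Under section 9.3 it is also the gate to the between-arm false-negative comparison and, after that, to D-dimer use and time in the emergency department. If efficacy power is well below 80%, the sponsor, funder and ethics committee are relying on a figure that the design cannot deliver, and the later tests inherit the shortfall.

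**Working it through.** **Inputs** (all from the protocol article): p1 = 0.45, p2 = 0.36, power 80%, ICC 0.05 (section 10.2); one-sided alpha 5% (sections 9.1 and 10.2); k = 10 centres per arm (section 5); 1280 patients per arm, hence 128 per centre (section 10.1).

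**Step 1: individual randomisation.** n = (1.645 + 0.842)² × (0.45×0.55 + 0.36×0.64) / 0.09² = 364.8 per arm, where the variance sum is 0.2475 + 0.2304 = 0.4779.

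**Step 2: trying to reproduce 2128.** With m patients per centre, the requirement is 10m = 364.8 × [1 + (m − 1) × 0.05] = 364.8 × (0.95 + 0.05m). The coefficient of m on the right is 364.8 × 0.05 = 18.24, larger than 10, so no positive m solves the equation. A finite answer needs more than 18.24 centres per arm.

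The nearest route to 2128 takes the centre size from the uninflated sample: m = 364.8/10 = 36.5, design effect 1 + 35.5 × 0.05 = 2.77, total 2 × 364.8 × 2.774 = 2024, and 2024/0.95 = 2130 after 5% loss. This is an inference about the source; the document does not show its steps. If it is the source, it is inconsistent with the design: 2128 patients in 20 centres is 106.4 per centre, with design effect 1 + 105.4 × 0.05 = 6.27. At 36.5 patients per centre, that total would need about 55 centres.

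**Step 3: power under the stated inputs.** SE = √(0.4779 × DE / n per arm), z = 0.09/SE, power = Φ(z − 1.645). The t version uses a non-central t with 18 df (20 centres minus 2).

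| Patients | m | DE | SE | z | Power (normal) | Power (t, 18 df) |
|---|---|---|---|---|---|---|
| 2128 | 106.4 | 6.27 | 0.0531 | 1.696 | 52.0% | 49.5% |
| 2560 | 128 | 7.35 | 0.0524 | 1.718 | 52.9% | 50.3% |
| unlimited | – | – | 0.0489 | 1.841 | 57.8% | 55.0% |

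The limiting SE is √(0.4779 × 0.05/10). The effective sample at 2560 patients is 1280/7.35 = 174 per arm, against the 365 needed. Simulation with beta-binomial centres agrees: 53% (normal) and 49% (t) at 128 per centre.

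**Step 4: ICC on the logit scale.** Section 10.2 does not name the scale. If 0.05 is a latent-scale value, the between-centre variance is (0.05/0.95) × π²/3 = 0.173 and the log odds ratio is 0.375. At 2560 patients, SE = √(2×0.173/10 + 1/(1280×0.2475) + 1/(1280×0.2304)) = 0.203 and z = 1.85, giving 58% (normal) or 55% (t). Treating the two rates as marginal rates and simulating gives up to 61%. The ceiling with unlimited patients is about 61–68%.

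**Step 5: what would give 80% at 2560 patients in 20 centres.**
- A residual ICC of at most about 0.020 (normal) or 0.018 (t).
- Or, at ICC 0.05, an intervention rate near 32%: a drop of 12.9 to 13.3 points, that is 12.9/45 = 29% to 13.3/45 = 30% relative, instead of 20%.
- For comparison, 2560 patients at ICC 0.05 would reach 80% with about 26 centres per arm.

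**Step 6: unequal centres.** With an assumed coefficient of variation of 0.6 in centre size (the document gives none) and near inverse-variance weighting, as in a mixed model, power at 2560 is about 51% (normal) or 49% (t). The loss is 1 to 2 points.

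**The case against.** The strongest defence is the stratification in section 5. Centres are stratified on their baseline imaging rate, which is a direct proxy for the between-centre variation that section 10.2 gives as its reason for choosing 0.05. If the analysis uses that factor, the residual ICC falls. A fall to 0.020 removes 1 − 0.020/0.05 = 60% of the between-centre variance and gives 80% at 2560. This stands as a possibility and belongs in the fix. It does not rescue 2128, because section 10.2 takes 0.05 as its planning value and claims no such reduction.

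It does mean that the ceiling is conditional. A reader might infer that no number of patients in 20 centres could ever exceed 58% power. The documents support that only for a proportion-scale ICC of 0.05 without baseline adjustment.

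Three further readings go too far:
- That unequal centre sizes cut power to about 42–44%. That figure weights centres by patient count; the planned mixed model does not, and with 128 patients per centre at this ICC a centre's precision depends little on its size.
- That the plan overstates a joint safety-and-efficacy power. It makes no joint-power claim, and its hierarchy allows a conclusion on safety alone.
- That a null result would be misread as absence of effect. That is speculation, since a confidence interval would show the imprecision.

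It might also be said that the mid-trial reassessment protects the power. It is triggered only by a control rate below 45% and changes only the sample size, whereas the limit here is set by the number of centres.

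**Conclusion.** The point holds. The figure of 2128, and the statement that 2560 patients are enough, are wrong on the plan's own inputs. Power for the imaging endpoint is about 49–52% at 2128 patients and 50–53% at 2560, with a ceiling of about 55–58% in 20 centres. These values rest on 45% versus 36%, a one-sided 5% test, 10 centres of equal size per arm, a proportion-scale ICC of 0.05 and no baseline adjustment. The logit-scale reading raises them to about 55–61% at 2560 and a ceiling of about 61–68%, still short of 80%. The reassessment after 1500 inclusions cannot secure 80% in 20 centres at this ICC.

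It does not follow that the trial cannot show an effect. A smaller residual ICC or a larger true reduction would restore the power, but the plan assumes neither.

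**What to change.** Rewrite section 10.2 before the first inclusion; the abstract says the trial has not started.

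1. Delete 2128 and the statement that 2560 is sufficient for efficacy. State the power as about 50–53% at 2560 patients, with a ceiling of about 55–58% in 20 centres, and name the scale of the ICC.
2. State that 80% holds only if the residual ICC is at most about 0.018–0.020, or if the true relative reduction is about 29–30%.
3. Estimate the between-centre variance from the pre-randomisation imaging survey in section 5 and report power at that value with a range. Twenty centres give an imprecise estimate: with 19 df, the 95% interval for a variance runs from 19/32.85 = 0.58 to 19/8.91 = 2.13 times the estimate, even ignoring sampling error within centres.
4. Prespecify adjustment of the mixed model for the centre's baseline imaging rate, already a stratification factor. State that about 60% of the between-centre variance would have to be removed to reach 80% at 2560.
5. State that the reassessment after 1500 inclusions cannot restore 80% by adding patients alone.

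The cost is a rewritten section and a less favourable power statement. The adjustment uses data already to be collected, and no extra patients are needed. If the sponsor wants 80% at ICC 0.05 without relying on adjustment, the effective lever is more centres, which is a separate and larger decision.

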## 6. Description of Study Intervention

### 6.1. Comparison Strategy: Control Group

The investigating physicians of the participating centers in the control group will be free to provide care as they see fit. However, a reminder of national and European guidelines for PE management will be given to them and they will have the recommendation to apply a validated strategy [3,4,5]. To make it easier, the different scores will be included in the clinical help–decision support software called SPEED [23]. Investigators will be asked to enter data about the included patients directly into SPEED, which will act as the study’s electronic case report form (eCRF). A paper version of the CRF will also be available. 

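### The 45% control imaging rate behind the efficacy sizing is weakly supported, and 2560 patients in 20 centres do not give the stated 80% power at that rate (about 53%)

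*Protocol article*

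**What the plan says.** Section 10.2 (Efficacy Endpoint) assumes "a usage rate of thoracic imaging of 45% in the control group", with "an alpha risk of 5%, a power of 80%, an intra-center correlation coefficient of 0.05" and 20 centres. The target is a 20% relative reduction, which is 9 percentage points at that rate. The calculation gives 2128 patients, and the section concludes that the 2560 required for safety will also cover efficacy. Both rates have one source: "We estimate that it will be 45% in the control group and 36% in the interventional group on the basis of a previous retrospective assessment". The citation is reference 15, which the Introduction also lists among its sources for this statement: "Assessed retrospectively based on large databases, the 4PEPS strategy seems to be more efficient and just as safe as the other strategies".

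The control arm is described in Section 6.1: "The investigating physicians of the participating centers in the control group will be free to provide care as they see fit". The text then qualifies this. Control physicians also receive a reminder of guidelines, a recommendation to apply a validated strategy, and the scores inside SPEED. In the other arm 4PEPS is likewise a recommendation (Section 6.2).

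Section 12 (Discussion) supports its savings argument with "the very high usage rate of CT angiographies (80% in a recent observational study [10"].

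Two features bear on the control rate. Section 5 has each centre assess its monthly volume and its imaging rate before randomisation, the purpose being a view "of the rate of imaging test performed in patients suspected of PE in order to have an accurate idea of their baseline status"; both measures serve as stratification criteria. Section 10.2 also plans to look at the control imaging rate after 1500 patients (750 control) and to reassess the sample size if the rate is below 45%.

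**The concern.** The effect is defined as a relative reduction, so the control rate fixes the absolute target: 20% of 45% is 9 points, 20% of 80% is 16 points. Both the target and the power follow from that one input. The plan takes it from a retrospective assessment, although the comparator is what emergency physicians actually do under light guidance. The only figure in the document tied to an observational study is nearly twice as high (80/45 = 1.8), and no sentence explains the gap.

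The figure at stake is the 80% power for the second step of the primary hierarchy. Superiority on imaging is tested once non-inferiority on safety is shown, and the secondary comparisons between arms follow only if superiority succeeds. If the stated power is wrong, the sponsor and the centres are relying on a chance of success that the design does not have.

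**Working it through.** **Inputs.** Control 45% and intervention 36%, one-sided alpha 5%, power 80%, ICC 0.05, 2128 patients (Section 10.2); 10 centres per arm (Section 5); 2560 patients, 1280 per arm (Section 10.1); one-sided tests (Section 9.1). Equal centre sizes are assumed, and no gain from stratification or covariates is modelled.

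**Step 1. Can 2128 be reproduced?** With individual randomisation, the pooled two-proportion formula gives n = 367 per arm. With k = 10 clusters per arm the requirement is

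N per arm = n(1 − ICC) / (1 − n × ICC / k),

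which has a solution only if n × ICC < k. Here 367 × 0.05 = 18.35, which exceeds 10. So no number of patients gives 80% power with 10 centres per arm. The published figure is approached only if the design effect uses the uninflated cluster size: 2 × 367 × [1 + (36.7 − 1) × 0.05] = 2044, or 2252 with a continuity correction (n = 389). Neither equals 2128. An ICC of about 0.018 in the correct formula would give 2124.

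**Step 2. Effective sample size at 2560.** Centre size is 1280/10 = 128. The design effect is 1 + (128 − 1) × 0.05 = 7.35. Effective n per arm is 1280/7.35 = 174.

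**Step 3. Power at 2560.** SE = √{[p0(1 − p0) + p1(1 − p1)]/174}, and power = Φ(d/SE − 1.645). For 45/36: SE = √(0.4779/174) = 0.0524, d/SE = 0.09/0.0524 = 1.72, and power = Φ(0.07) = 53%. The last column uses a noncentral t with 18 degrees of freedom.

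| Control / intervention | Difference | Power, normal | Power, t (18 df) |
|---|---|---|---|
| 45% / 36% (plan) | 9 points | 53% | 50% |
| 60% / 48% | 12 points | 73% | 70% |
| 70% / 56% | 14 points | 86% | 84% |
| 80% / 64% | 16 points | 96% | 95% |
| 80% / 71% | 9 points | 62% | 60% |

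At 2128 patients the design effect is 1 + (106.4 − 1) × 0.05 = 6.27, effective n is 170, and power at 45/36 is 52%.

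**Step 4. Ceiling at 45/36.** With unlimited patients in 10 centres per arm, effective n tends to 10/0.05 = 200 and power to about 57.5%. The number of centres and the ICC limit power; extra patients hardly help.

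**Step 5. Optional sensitivity.** The document gives no adherence figure. If, as an assumption, the 9-point difference is reached in only 80% of intervention patients and the rest are imaged at the control rate, the difference is 0.8 × 9 = 7.2 points and power is 39% (t: 37%). At 60% it is 5.4 points and 27% (t: 25%).

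**The case against.** A reader might infer that 80% is the true control rate and that the trial is sized for the wrong comparator. The documents do not support that. The 80% comes from one cited study and appears as background in the Discussion. It counts CT angiography, whereas the endpoint also includes scintigraphy, and nowhere is it called the rate expected in these 20 centres. Control physicians are not left unaided either: the reminder, the recommendation and SPEED may all lower imaging. Section 12 reports that SPEED improved diagnostic management in a randomised study. A rate derived from validated strategies is therefore not plainly wrong for this arm.

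A reader might also infer that a higher control rate would undermine the sizing. At the planned 20% relative reduction it does the opposite. Even with the difference held at 9 points, 80/71 gives 62%, more than the 53% at 45/36.

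It is also tempting to say that the 45% and 36% describe rules applied to every patient on paper. That is an inference from the Introduction, since the cited source is not at hand.

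Finally, the interim look at the control rate is a real safeguard, and it acts in the direction in which a fixed relative reduction loses power. All these points stand. They do not explain why 45% was chosen, and they do not restore the 80% power. The interim look is triggered only below 45%, so a control rate at or above 45% prompts no re-sizing even though power at exactly 45% is already about 53%.

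**Conclusion.** The concern holds in a limited form. The control rate rests on a retrospective assessment, is not reconciled with the 80% in the Discussion, and strongly affects power. Across control rates from 45% to 80% with a 20% relative reduction, power at 2560 patients runs from 53% to 96%. At the plan's own inputs it is about 53% (50% with the t distribution), some 27 points below the stated 80%. That shortfall comes from an ICC of 0.05 with 10 centres per arm, whatever the source of the 45%. The unsupported control rate adds uncertainty in both directions and does not by itself show that the trial is underpowered.

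The result assumes equal centre sizes, a standard design effect and no gain from stratification. A true ICC well below 0.05 would raise the power.

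**What to change.** Before the first inclusion, revise Section 10.2 as follows:

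- Base the control rate on the pre-randomisation audit of Section 5, measured with the definition of the primary efficacy endpoint. State that the audit precedes the control-arm reminder and recommendation, so it may overstate imaging under trial conditions.
- Give the absolute target as 20% of that rate.
- Report the power achieved at 2560 patients with 20 centres and ICC 0.05. If it is below 80%, withdraw the statement that 2560 is enough for this endpoint.
- Say why 45% was expected if it is kept. In Section 12, explain the 80% or remove it from the savings argument.
- Adherence scenarios may be added as sensitivity figures, labelled as assumptions.

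The cost is one recalculation and a few sentences, since the audit is already planned. Making the correction requires no change in enrolment, because 2560 is set by the safety endpoint. The drawback is that the stated efficacy power may become less favourable.
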